### Specific objectives

The specific objectives of this study are as follows:To compare the occurrence rates of early 30-day post-operative complications (pain, hematoma, surgical site infection) following euthyroidectomy under LA versus GATo compare the cost implications of euthyroidectomy under LA versus GATo compare the patients’ level of satisfaction for euthyroidectomy under LA versus GA

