### Primary outcome measures

The primary outcome measures will be early 30-day post-operative complications (harms), including: pain, nausea, vomiting, hematoma, transient voice changes, and surgical site infection rates.

The complications will be reported verbally to nursing or to attending physicians for evaluation and recorded on a questionnaire in accordance with MedDRA® version 4.21 standardized reporting on medical and surgical procedures. The post-operative pain will be measured based on visual analogue scale of 0–10 where 0 means no pain and 10 means the worst possible pain. The pain will be assessed at an interval of 6, 12, and 24 h and at 30 days. The mean pain scores will be compared at using Student’s *t*-test, assuming normal distribution; otherwise, medians will be compared using non-parametric Kruskal–Wallis rank sum test.

The nausea and vomiting will be reported to nursing or attending physicians and recorded to the questionnaire using a nausea score on a scale of 0–9 where 0 means no symptom and 9 means very severe. The symptoms will be assessed at an interval of 6, 12, and 24 h and at 30 days. The mean nausea scores will be compared using a paired Student’s *t*-test, assuming normal distribution; otherwise, medians will be compared using non-parametric Kruskal–Wallis rank sum test.

Complications: hematoma, transient voice changes, and surgical site infection rates will be assessed at 6, 12, and 24 h and at 30 days will be reported in accordance with the Clavien Dindo classification of surgical complications [27], where grade I represents complications that do not require any additional intervention, grade II requires pharmacological treatment but not radiological or surgical intervention for instance blood transfusion, grade III requires radiological or surgical re-intervention, e.g., neck exploration and hematoma evacuation, grade IV representing life-threatening complications with at least one organ dysfunction such as respiratory failure that requires intensive care admission. The difference in proportions will be compared using Wilcoxon sum rank test.

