### Methods: assignment to treatment arms

This study will be a parallel trial where different groups will be randomly allocated to receive different interventions concurrently during the study.

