### Randomization, blinding and allocation concealment and implementation

Patients who meet the inclusion criteria will be assigned randomly by research assistants to either local anesthesia group (L) or general anesthesia group (G) using envelope concealment. Half of these concealed envelopes will contain letter L and the other half letter G to represent LA and GA, respectively. Permuted balanced block randomization will be performed by the study supervisor to derive a random sequence of numbers that will represent the two arms in an allocation ratio of 1:1. The random sequence numbers will be generated using a web-based software (https://www.random.org/). A set of 52 numbers will be generated beginning with a minimum of 1 and maximum of 52. The numbers will then be used to label the sealed envelopes sequentially and will be concealed to research assistants. The content of the envelope will be concealed only to be opened in the operating room for the anesthesia providers to know what anesthetic technique is to be used for the research participant.

The study participants at this point in the operating room will not be blinded as the research and ethics committee considered it a moral obligation for patients to understand the nature and risks of anesthesia techniques to be used on them prior surgery.

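### Nausea scores, part of the primary outcome, are assigned a paired t-test although the two arms are independent parallel groups

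*Protocol article*

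**What the plan says.** All places are in the protocol article.

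- *Primary outcome measures* defines the primary outcome as 30-day complications, "including: pain, nausea, vomiting, hematoma, transient voice changes, and surgical site infection rates". Nausea is scored 0–9 at 6, 12 and 24 hours and at 30 days.
- The test named for that score is: "The mean nausea scores will be compared using a paired Student’s *t*-test, assuming normal distribution". If normality fails, "otherwise, medians will be compared using non-parametric Kruskal–Wallis rank sum test".
- For pain, with the same schedule and the same fallback, the section says: "The mean pain scores will be compared at using Student’s *t*-test, assuming normal distribution". Pairing is not mentioned.
- *Methods: assignment to treatment arms* gives the design: "This study will be a parallel trial where different groups will be randomly allocated to receive different interventions concurrently during the study".
- The allocation section (*Randomization, blinding and allocation concealment and implementation*) describes permuted blocks "to derive a random sequence of numbers that will represent the two arms in an allocation ratio of 1:1". It describes no matched pairs.
- *Specific objectives* sets the contrast as LA versus GA: "To compare the occurrence rates of early 30-day post-operative complications".
- *Objective one* names a two-sample Student's t-test for complication proportions.

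**The concern.** A paired t-test analyses within-pair differences, so each observation in one group needs a natural partner in the other. Here the groups are different, unmatched people. Two readings of the sentence are possible, and neither works.

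- **Paired between arms.** Someone must decide which LA patient goes with which GA patient. The design gives no rule, so sort order decides, and with it the p-value. If the numbers analysed differ between arms, some patients also have to be left out.
- **Paired within patient over time.** The test then describes change in nausea and says nothing about LA versus GA.

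At stake is the inference on one of six listed components of the primary outcome. Two analysts with the same data could report different p-values and both claim to have followed the protocol.

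**Working it through.** **1. Is there any pairing to use?** The arms are parallel, allocation is of individuals in permuted blocks, and no matched-pair randomization or planned second treatment period appears. The crossover mentioned under *Individual discontinuation* is conversion of an LA patient to GA during surgery. A within-patient reading also finds no support: no baseline nausea score or time contrast is named, four assessment times do not suit one paired t-test, and the fallback (Kruskal–Wallis) is a test for independent groups. As written, the sentence prescribes a paired test if scores are normal and an independent-groups test if they are not.

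**2. Does the planned sample size assume pairing?** No. Two independent proportions (0.83 and 0.79), margin 0.33, one-sided alpha 0.05 and 80% power give

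n = [0.83×0.17 + 0.79×0.21] × (1.645 + 0.842)² / (0.33 − 0.04)² = 22.6, so 23 per arm.

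Then 23/0.90 = 25.6, so 26 per arm. This reproduces the stated 26. The one-sided alpha is an assumption, as the article does not give sidedness. The trial was sized for two independent arms.

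**3. What does an arbitrary pairing do to the statistic?** With n per arm, equal SDs s and mean difference D:

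- independent test: t = D / √(2s²/n), with 2n − 2 = 50 degrees of freedom, critical value 2.009;
- paired test: t = D / √(2s²(1 − r)/n), with n − 1 = 25 degrees of freedom, critical value 2.060.

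So the paired t equals the independent t divided by √(1 − r), where r is the sample correlation created by the pairing. With unmatched patients, r is noise. Over random pairings of 26 it has mean 0 and SD 1/√25 = 0.20, so about 95% of values lie within ±0.392.

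Take data with an independent t of 2.009 (p = 0.050):

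| r from the pairing | paired t | paired p (25 df) |
|---|---|---|
| +0.392 | 2.009/√0.608 = 2.576 | 0.016 |
| 0 | 2.009 | 0.056 |
| −0.392 | 2.009/√1.392 = 1.702 | 0.101 |

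Paired p falls below 0.05 when r exceeds 1 − (2.009/2.060)² ≈ 0.049. By the normal approximation this happens in about 40% of pairings (0.049/0.20 = 0.24 SD).

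**4. Check by simulation** (normal scores, 26 per arm, two-sample p about 0.05, 5,000 random re-pairings per data set). One data set gave a central 95% range for paired p of 0.016 to 0.098, median 0.054, with 44% below 0.05. A second gave 0.017 to 0.102, median 0.055, full range 0.003 to 0.128. Both agree with the table.

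**5. Long-run error rates under one arbitrary pairing** (20,000 runs, 26 per arm, normal scores):

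| | independent | paired |
|---|---|---|
| type I error at 0.05 | 0.051 | 0.052 |
| power at a standardized difference of 0.8 | 0.81 | 0.80 |

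The two tests reach the same decision in about 98% of runs with no difference, 93% at a standardized difference of 0.56 and 95% at 0.8.

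**The case against.** The strongest case on the other side accepts that the word is wrong and argues that little follows from it.

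- **It looks like a slip.** The fallback, the plain t-test for pain and the two-sample test under *Objective one* all point to an unpaired comparison. That is probably the intent. But *Objective one* speaks of proportions, so it does not override the explicit instruction for the nausea score. Nor is the pain test expressly called unpaired.
- **The fallback may usually apply.** If many patients score zero, normality will tend to be rejected. With 26 scores and the non-zero values spread evenly over 1–9, the Shapiro–Wilk test rejects in about 80% of samples with 20% zeros, and in nearly all with 50% zeros. The article gives no nausea distribution, so this is illustrative. It stands as a limit on how often the error takes effect: the consequence is conditional on the t-test being used.
- **Error rates hardly move.** True, as step 5 shows. The 44% also comes from a data set placed at p = 0.05, where a near-even split is expected. This rules out a claim of inflated error. It does not answer the point that the result depends on list order, which can be chosen after the data are seen.
- **Unequal arms may not arise.** *Missing data* plans imputation, and the analysis set is all eligible randomized patients, so arms could stay near 26 and 26. The point about dropping patients is therefore conditional. Imputation still creates no valid pairs.

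**Conclusion.** The concern holds. The test named for a component of the primary outcome does not fit the parallel-group design, and it conflicts with its own fallback in the same sentence. Whenever the t-test is used, the p-value either depends on an arbitrary ordering of patients or answers a within-patient question that the trial does not ask. For data near the 0.05 boundary at 26 per arm, paired p can fall anywhere from about 0.016 to 0.10 by ordering alone. Away from that boundary the decision seldom changes. Average type I error and power are essentially unaffected, and so is the sample size. These figures assume normal scores, equal SDs and the stated standardized differences, because the article gives no SD for nausea. That the test is wrong for the design rests on none of these assumptions.

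**What to change.** In *Primary outcome measures*, replace the paired t-test for nausea with an independent two-sample test. Either of these would do:

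- a Welch two-sample t-test; or
- the Wilcoxon rank-sum test, which suits a bounded 0–9 score and, for two groups, is equivalent to the Kruskal–Wallis fallback already named.

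Report the LA minus GA difference with its confidence interval at each time point. State in the pain sentence that its t-test is also for independent groups, so that the two scores are handled alike.

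The core correction is one word; the choice of Welch and the interval add a short clause. Neither changes the number of patients, the assessments or the data collected. The correction should be made before any unblinded data are analysed, including at the interim look. It settles only which test compares the arms: a test of no difference would not by itself show equivalence on this score.

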### Secondary outcome measures

The average procedure costs in USD and mean duration of hospital stay (number of days away from work) will be recorded based on extracts from the patients’ case files and compared between the two anesthetic techniques.

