Following the advancement of general anesthesia (GA) techniques in which a state of unconsciousness is induced with complete absence of pain and reflexes, the number of thyroidectomies performed under GA increased and ultimately, GA became the preferred method under which thyroidectomy is carried out. In the current surgical practice, majority of surgeons prefer to perform thyroidectomy under GA which offers the advantage of pain-free surgery to the patient, thus reducing their anxiety and enabling a more relaxed operating room environment for the surgeon [8, 9].

Conversely, preference to GA is not without limitations. First, the longer recovery time from anesthesia results in prolonged hospitalization, delayed return to work, reduced patient turnover, and ultimately contributes to the unmet need for surgery. This culminates in patients presenting much later in life with huge goiters that have both local and systemic complications, compromising their general well-being, quality of life, and economic productivity. Secondly, in low-income settings with limited infrastructural and human resources, GA is comparatively undesirable due to concerns related to post-operative care and monitoring after the surgery such as lack of skilled staff and equipped intensive care units [6]. For instance, despite efforts from donor funding and south-west institutional collaborations, Uganda with its 45 million population boosts with only 100 qualified anesthesia providers (fewer than 0.05 anesthesia providers per 100,000 population) as opposed to high-income settings such as the UK with over 18 per 100,000 population [12]. Therefore, performing thyroidectomy under LA would offer the advantage of the anesthesia being administered by the surgeons themselves without putting much strain on the weak health systems.

Henceforth due to drawbacks of GA, in the last two decades, there has been an increase in the number of thyroidectomies performed under regional/LA combined with monitored anesthesia care [11, 13]. These numbers have even increased further with the development of minimally invasive thyroidectomy particularly in short-stay settings [9] and now, a few surgeons in the western world are currently doing thyroidectomies exclusively under LA [8].

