### Interventions: description/study procedure

Eligible participants based on our screening log will sign an informed consent document and undergo pre-anesthetic assessment 24 h prior surgery. This assessment will be undertaken in the designated tents used for our camp settings. All participants will be subjected to the Bulamu Healthcare fasting protocol of 6 and 2 h for solid and liquid diet respectively and will receive 1 g of intravenous ceftriaxone 60 min prior surgery. It is also a routine practice in Bulamu Healthcare to record all patients’ vital signs at 24 and 0 h prior surgery. These include but not limited to pulse rate, oxygen circulation, blood pressure, and ECG monitoring. All procedures are carried out under aseptic techniques. Following the procedure, all participants will receive intramuscular injection of diclofenac sodium 7 mg stat followed by 100 mg of oral diclofenac sodium 8 hourly for 5 days. Patients will be discharged home when they score at least 9 post anesthesia discharge scoring system [25] at the discretion of attending clinicians. Review at the 30th day will be in outpatient setting upon call by the outcome assessors. Telephone follow-up interview assessment option will be available for those who will reasonably be unable to attend an outpatient visit.

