## Objective two

The cost of euthyroidectomy done under LA and GA will be estimated by the would-be expenditure on drugs and sundries based on national drug authority (NDA) quotation. The admission costs will be calculated in form of number days of admission (away from duty/work as cost) and bed occupancy for the two arms.

The average cost incurred on patients operated either under the LA or GA from admission till discharged will be calculated and compared. The difference in the average cost between the two arms will be compared using *t*-test, assuming normal distribution.

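### Inpatient days from case files are labelled and costed as days away from work, which leaves out any work lost after discharge

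*Protocol article*

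**What the plan says.** The definition appears twice in the protocol article. Secondary outcome measures states: "mean duration of hospital stay (number of days away from work) will be recorded based on extracts", the source of the extracts being the case files. Objective two carries it into cost: "The admission costs will be calculated in form of number days of admission (away from duty/work as cost) and bed occupancy". The same section fixes the window, since average cost per patient "from admission till discharged will be calculated and compared".

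Three other places bear on this:

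- **Introduction.** Among the drawbacks of GA it lists "prolonged hospitalization, delayed return to work, reduced patient turnover", as separate items.
- **Interventions: description/study procedure.** On leaving hospital: "Patients will be discharged home when they score at least 9 post anesthesia discharge scoring system". On later contact: "Review at the 30th day will be in outpatient setting upon call by the outcome assessors", with a telephone interview for those who cannot attend.
- **Table 1 (SPIRIT timeline).** The row for cost implications is marked at 6, 12 and 24 h and again at 30 days.

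**The concern.** Length of stay runs from admission to discharge. Work absence runs until the patient is back at usual work. The two are equal only if every patient resumes work on the day of discharge. The protocol gives the first quantity the name of the second, takes it from inpatient records, and uses it as the work-loss element of cost.

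At stake is what can be said about lost work under objective two. If the plan is followed as written, a report could state that the arms lost the same number of work days when all that was compared was time in hospital. LA and GA might differ in recovery at home, and the figure could not show it.

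**Working it through.** The protocol gives no figure to reproduce, so the check sets the sections side by side and follows the algebra.

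**Step 1: is the stay–work equation a stray phrase?** No. It stands in the outcome definition and again in the analysis text for Objective two, where admitted days are the stated measure of time off work.

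**Step 2: do the protocol's own rules make the two quantities equal?** No. Discharge depends on a post-anesthesia discharge score, with clinician discretion. That rule concerns readiness to go home; nothing in it concerns fitness for work. The Introduction also treats the two as distinct.

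**Step 3: is work absence collected elsewhere?** No section says so. The Data collection section says Part D of the questionnaire is completed after surgery and during follow-up, but the questionnaire is not shown. Table 1 marks cost at 30 days without naming a work-day item.

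**Step 4: what does the equation do to the comparison?** For one arm let

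- s = mean days admitted,
- r = mean work days lost after discharge.

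True work absence is s + r; the plan counts s. With subscripts G and L for the arms:

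- true difference = (s_G − s_L) + (r_G − r_L)
- counted difference = s_G − s_L
- amount omitted = r_G − r_L

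If a work day is valued at w, the work-loss part of the cost difference is wrong by w × (r_G − r_L). The protocol gives no value for s, r or w.

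**Step 5: illustration with assumed values.** Share of one arm's work absence that is counted, s/(s + r):

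| Assumed r (days) | s = 1 | s = 2 |
|---|---|---|
| 0 | 1/1 = 100% | 2/2 = 100% |
| 3 | 1/4 = 25% | 2/5 = 40% |
| 7 | 1/8 = 12.5% | 2/9 = 22% |
| 14 | 1/15 = 7% | 2/16 = 12.5% |

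This share describes how far the label misstates the level within an arm. It is not the bias in the comparison, which is r_G − r_L alone. With equal stay in both arms, a difference in post-discharge recovery of 0 days would be recorded correctly as 0, while an assumed difference of 2 or 3 days would also be recorded as 0.

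**Step 6: cost window.** Objective two closes the window at discharge, but Table 1 schedules a cost assessment at day 30, when most patients will presumably be home. Both cannot describe the same cost outcome without further explanation.

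**The case against.** The strongest reply is that this is loose wording in a legitimate design.

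- **A length-of-stay outcome should stop at discharge.** This stands in full. A reader might infer that the stay outcome itself is defective because it counts post-discharge days as zero. The protocol does not support that; only the work label and the costing are at fault.
- **Admission to discharge is a recognised costing perspective.** This also stands. The cost studies described in the Introduction use similar scopes, and one is described in almost the same terms. A trial may leave out productivity loss altogether.
- **Objective two can be read as valuing each admitted day as a day off work, without claiming that this is all the work lost.** That reading is possible for Objective two. It does not rescue Secondary outcome measures, where the bracket equates the two quantities outright.
- **Return to work is not a stated objective.** Correct. The Specific objectives name complications, cost implications and satisfaction, and delayed return to work appears only as background. A reader might infer that the trial fails to answer a question it set itself; that goes too far. It did, however, choose to treat time off work as a cost, and a chosen component should be measured as named.
- **The 30-day cost mark and Part D of the questionnaire may capture more.** They may, so it cannot be said that post-discharge work loss is certainly unrecorded. But neither is said to include work days, and the stated source for this outcome is the case file.

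Nor does the point rest on detail that an article would leave to a fuller document. The article states the definition, the source and the window.

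**Conclusion.** The point holds as a labelling and costing fault in secondary outcomes. Inpatient days are a valid measure of stay and an invalid measure of work absence. Used as the latter, they omit r in each arm and r_G − r_L from the comparison.

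The size cannot be given. It depends on post-discharge recovery in each arm, for which the documents have no data; the percentages above are illustrations only. A reader might infer that most work loss is missed, or that the LA–GA contrast is biased in a known direction. Neither is supported: if recovery at home is equal in the two arms, the contrast is unbiased even though the levels are mislabelled.

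The conclusion assumes that case-file extracts end at discharge, which is an inference, though it agrees with the stated cost window. The sample size and the primary outcome are unaffected.

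**What to change.** 1. In Secondary outcome measures, define length of stay as admission to discharge, taken from the case file, and delete the bracket that equates it with work absence.
2. In Objective two, cost bed-days from that measure and stop using admitted days as the count of work days lost.
3. If lost work is to be costed, add a separate outcome: days from surgery to return to usual work, asked at the day-30 review or call and censored at 30 for those not yet back. Report and cost it apart from bed-days.
4. State whether the cost window closes at discharge or at day 30, and bring Objective two and Table 1 into line.

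Items 1, 2 and 4 are wording changes. Item 3 costs one question at a contact already planned; its small downsides are self-report and censoring at day 30. The Study period section makes May 2023 the last follow-up month. If follow-up has closed without that question, the minimum is to report the figure as length of stay and make no claim about work days lost.
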